## Abstract

**Background:**

Vietnam has a smoking prevalence that is the second highest among Southeast Asian countries (SEACs). According to the World Health Organization (WHO), most reductions in mortality from tobacco use in the near future will be achieved through helping current users quit. Yet, largely due to a lack of research on strategies for implementing WHO-endorsed treatment guidelines in primary care settings, services to treat tobacco dependence are not readily available to smokers in low middle-income countries (LMICs) like Vietnam. The objective of this study is to conduct a cluster randomized controlled trial that compares the effectiveness of two system-level strategies for implementing evidence-based guidelines for the treatment of tobacco use in 26 public community health centers (CHCs) in Vietnam.

**Methods/Design:**

The current study will use a cluster-randomized design and multiple data sources (patient exit interviews, provider and village health worker (VHW) surveys, and semi-structured provider/VHW interviews) to study the process of adapting and implementing clinical practice guidelines in Vietnam and theory-driven mechanisms hypothesized to explain the comparative effectiveness of the two strategies for implementation. CHCs will be randomly assigned to either of the following: (1) training plus clinical reminder system (TC) or (2) TC + referral to a VHW (TCR) for three in person counseling sessions. The primary outcome is provider adherence to tobacco use treatment guidelines. The secondary outcome is 6-month biochemically verified smoking abstinence.

**Discussion:**

The proposed implementation strategies draw on evidence-based approaches and a growing literature that supports the effectiveness of integrating community health workers as members of the health care team to improve access to preventive services. We hypothesize that the value of these implementation strategies is additive and that incorporating a referral resource that allows providers to delegate the task of offering counseling (TCR) will be superior to TC alone in improving delivery of cessation assistance to smokers. The findings of this research have potential to guide large-scale adoption of promising strategies for implementing and disseminating tobacco use treatment guidelines throughout the public health system in Vietnam and will serve as a model for similar action in other LMICs.

**Trial registration:**

NCT01967654

**Electronic supplementary material:**

The online version of this article (doi:10.1186/s13012-015-0328-8) contains supplementary material, which is available to authorized users.

## Background

Almost half of adult men in Vietnam are current smokers, a smoking prevalence that is the second highest among Southeast Asian countries (SEACs) [1]. If current smoking rates are not addressed, it is estimated that in 10 years, tobacco use will be responsible for about 25 % of adult male deaths in Vietnam [2]. Most reductions in mortality from tobacco use in the near future will be achieved through helping current users quit [3, 4]. Encouragingly, two thirds of current smokers in Vietnam are planning to or thinking about quitting and over half attempt to quit annually [1].

**Fig. 1 Fig1:**

Study design

**Fig. 2 Fig2:**
[figure not shown]
Conceptual framework

Tobacco use treatment, as defined by the U.S. Preventive Health Service Guideline (PHS Guideline) on *Treating Tobacco use and Dependence*, is evidence-based and highly cost-effective [5]. The Guideline, which is endorsed by the World Health Organization (WHO), is based on a meta-analysis of over 8000 studies and provides strong evidence that asking all patients about tobacco use, advising smokers to quit, assessing readiness, providing assistance, and arranging follow-up (the 5As) can significantly increase smoking abstinence rates [5]. Yet, adoption of guideline-recommended care into routine public health and clinical practice in low middle-income countries (LMICs) is suboptimal [6, 7]. This is in large part due to a lack of research on strategies for implementing evidence-based tobacco use treatment guidelines.

Implementing evidence-based tobacco use treatment is a core provision in the WHO Framework Convention on Tobacco Control (FCTC). The FCTC is an evidence-based treaty that was developed by the WHO in response to the globalization of the tobacco epidemic [8]. The FCTC regulatory strategies include implementing evidence-based smoking cessation treatment in public health care delivery settings. In fact, Article 14 of the FCTC states that “each country shall take effective measures to promote cessation and adequate treatment for tobacco dependence” [9]. Although Vietnam has a strong public health delivery system, according to the 2010 Global Adult Tobacco Survey, like other SEACs, services to treat tobacco dependence are not readily available to smokers [1]. Barriers to integrating treatment into routine primary care in LMICs are similar to those in the USA and include the following: (1) inadequate training of health care providers, (2) lack of evidence-based systems for implementing guideline recommended care, and (3) a lack of research on strategies for implementing tobacco use treatment guidelines in LMICs [10].

Closing the gap between research and practice is stymied by limited research on cost-effective strategies for integrating cessation services into routine practice. Drawing upon a burgeoning implementation science literature [11–17] and a growing literature that supports the effectiveness of integrating community health workers as members of the health care team to improve access to preventive services [18–24], we propose to compare the effects of two organization-level strategies: (1) training and a clinical reminder system (TC) vs. (2) TC + referral (TCR) to community health workers (CHW), referred to as village health workers (VHW) in Vietnam, for additional counseling and support. The PHS Guideline strongly recommends staff training and clinical reminder systems as the foundation for increasing adherence to guideline-recommended care [5]. However, several studies have shown that adding a referral system can enhance rates of provider adherence to tobacco use treatment guidelines and increase smoking abstinence rates beyond that of training and clinical reminders alone [13–16]. The impact of referral systems on adherence to tobacco use treatment guidelines is also supported by a recent study in Malaysia [25]. This study, conducted in diabetes clinics, similarly found that providing a referral to stand-alone cessation clinics motivated clinicians to routinely provide cessation advice. Therefore, offering a referral option for additional counseling may enhance quit attempts and cessation rates. However, the Malaysian model of creating stand-alone cessation clinics is too expensive to disseminate widely and stands in contrast to recommendations from the WHO’s recently published guidelines for implementing Article 14 which states: “In order to promote tobacco cessation and develop tobacco dependence treatment as rapidly as possible and at as low a cost as possible, countries should use existing resources and infrastructure” [9].

This proposal leverages existing infrastructure elements, including a robust public health care delivery system with an extensive network of VHWs in Vietnam. In Vietnam, as in other LMICs, VHWs have a strong track record of effectively delivering preventive services and increasing the reach of these programs [18, 20]. As a critically important member of the public health care system, it is surprising that in LMICs, there are no studies evaluating the role of community health workers as a referral resource for increasing access to evidence-based smoking cessation services, and we are aware of only one study in the USA [19]. Consistent with WHO Guidelines for implementing Article 14, CHWs offer a sustainable resource for ensuring wide access to support for tobacco users who wish to quit. Using a two-arm cluster randomized control trial design, the aims of this study are to (1) compare the effectiveness and cost-effectiveness of two multi-component strategies for implementing tobacco use treatment guidelines and (2) use a mixed methods approach to explore potential theory-driven mechanisms hypothesized to explain the comparative effectiveness of the implementation strategies.

## Methods

### Study setting

The Vietnamese health care system is hierarchically organized into four administrative levels: central, province, district, and community. At the central level is the Ministry of Health (MOH), the main national authority in the health sector, which formulates and implements national health policies and programs. The provincial-level health system consists of Provincial Health Departments and Preventive Health Centers, which are administered by the Provincial People’s Committee in each province. At the district level, the District People’s Committee administers district health centers and district-level hospitals. Within districts, the community health centers (study sites for this research) serve as the primary access point for public health and preventive care services in Vietnam, each providing services for an average of 3000–15,000 people in their surrounding community. CHCs are charged with implementing more than 10 national health programs, treatment of common diseases, provision of health counseling and education, referral services, pre- and post-natal care, family planning, and food hygiene and safety. Each CHC is staffed by 5–6 clinicians, including 1 physician and 3–5 other health professionals (nurses, midwives). In addition, each CHC is supported by a network of 8–20 VHWs who provide counseling and education to implement national health programs at the village level and serve as clinician extenders to ensure patients are adhering to clinician-recommended care. VHWs are under the direct management and direction of the CHCs and coordinate with community and social organizations in the village.

### Study design

We are conducting a two-arm, cluster randomized controlled trial comparing (1) training and clinical reminder system (TC) vs. (2) TC + referral to a VHW (TCR) for additional counseling (Fig. 1). The primary outcome is improvement in provider adherence to tobacco use treatment guidelines which has been found through extensive meta-analysis to be an essential determinant of patient cessation outcomes [5]. The secondary outcome is 6-month biochemically verified smoking abstinence rates. Finally, guided by Damschroeder’s Consolidated Framework for Implementation Research and Weiner’s organizational model of innovation implementation, we will explore external (e.g., national and district level policy) and internal setting constructs (e.g., organizational readiness) that may influence the relationship between the implementation strategies and implementation effectiveness [26–29].

### Study site eligibility and recruitment

We are recruiting 26 health centers in Thai Nguyen, a rural province north of Hanoi. Thai Nguyen has 9 districts with 180 CHCs. Site criteria include having at least one physician, ≥4 allied health care professional staff, ≥5 VHWs, and a patient population of at least 3000. Site recruitment started with in-person site visits with the Director of the District Health Centers to introduce the study and to obtain a list of CHCs that fit these criteria. Among those expressing interest, we randomly selected 26 CHCs. For practical reasons (cost and staffing), clinic sites will be recruited in 3 successive waves with 8 in the first wave, 10 in the second, and 8 in the third wave.

### Conceptual framework

Our proposed study draws on the Consolidated Framework for Implementation Research (CFIR) to inform the analysis of factors that influence effective implementation (i.e., provider adherence to tobacco use treatment guidelines) and Weiner’s model for implementation effectiveness [26, 27, 29] (Fig. 2). Similar to the socio-ecologic model, CFIR acknowledges that the effectiveness of interventions implemented within a health system is influenced by the interaction of environmental/policy within the larger health care system in Vietnam, organizational (e.g., organizational readiness), and individual-level factors. Therefore, CFIR organizes constructs into domains that include (a) intervention characteristics, (b) outer setting, (c) inner setting, and (d) individual (patient and provider) characteristics. Wiener et al.’s model addresses “inner setting” or organizational factors positing that implementation strategies (i.e., TC and TCR) enhance implementation effectiveness *through* changes they produce in the implementation climate (i.e., means, opportunity, and expectation) and the extent to which providers perceive that delivering guideline-concordant tobacco use treatment fits their values (i.e., attitudes) and local task requirements (e.g., workload and workflow). ARM 1 (TC) is expected to promote a positive implementation climate by enhancing providers’ perception that tobacco use treatment is a *priority* and by providing the *means* (i.e., new knowledge through training) for adhering to guideline-recommended care. We hypothesize that the addition of a VHW referral system (ARM 2) will result in rates of provider adherence that are superior to ARM 1 through additional changes in perceived *means*, *opportunity*, *and* enhanced *task fit* (i.e., referral system offers providers’ an opportunity to delegate counseling and follow-up).

### Description of intervention conditions

#### ARM 1: provider and staff training and clinical reminder system (TC)

##### Staff training

All clinical and support staff will attend a 2-day training in the use of the 5As and the intervention protocol, including how to make a referral to the VHW (for those in ARM 2). The training is based on the PHS Guideline *Treating Tobacco use and Dependence*, the WHO’s recently released training package for building capacity for tobacco control in primary care and addresses core competences defined by the Association for the Treatment of Tobacco Use and Dependence (http://attudaccred.org/) [5, 30]. Training will be conducted by [name] and [name] (MPIs). We will conduct pre- and post-surveys to assess changes in knowledge and to assess satisfaction with the training. A 1-day booster training will be conducted at 3 months after the start of the intervention to address challenges, review screening and counseling techniques, and review documentation procedures.

##### Clinical reminder system and toolkit

The reminder system is designed to remind the intake clinician to assess smoking status, assess readiness, and offer each smoker brief cessation counseling. Given the lack of charts in the CHCs, this component of the intervention was adapted to include posters prompting providers to ask about tobacco use, advice patients to quit, and for sites in the referral arm of the study, to refer patients to the VHW (Additional file 1). Additional materials were developed as part of a larger toolkit to support provider and patient behavior change. These include a table tent provides guidance for providers on how to offer brief counseling and three-patient self-help brochures (dangers of secondhand smoke, health effects of smoking, and creation of a quit plan).

#### ARM 2: TC + referral to VHW

##### Referral to VHW

Based on our pilot research, we created a referral form that is similar to the one we have tested in the USA [16, 17]. For smokers who are interested in quitting and agree to be referred for counseling, the form is completed by the CHC staff. VHWs will then pick up the forms at their regular weekly meetings at the CHCs. Smokers will be contacted within 5 days of their visit to schedule the first of three counseling sessions. The sessions are conducted in person and will last approximately 30 min. The first session will be conducted within 1 week of the patient visit to the CHC (planning session) and the second and third sessions at 2 (within 2 days of quit date) and 4 weeks post-clinic visit. The counseling schedule is based on the PHS Guideline, our pilot data, and evidence that early more intensive contact around the quit date is associated with improved cessation rates [5, 31, 32]. Counseling will focus on motivational barriers for treatment readiness and offer stage-based cessation advice. Motivational interviewing (MI) techniques have been found to be effective in increasing abstinence and quitting attempts [33]. There is also evidence that lay health workers can be trained to offer effective MI [34]. Six VHWs from each intervention clinic will be invited to participate in a 4-day training that will build on the provider training to ensure proficiency in motivational techniques. The MI module was adapted from an existing curriculum and pretested in two focus groups with VHWs. Standardized training, setting performance criteria, and conducting a booster session will help ensure intervention fidelity. In addition, each VHW will have a field manual, which will have all of the information necessary for completion of the intervention components as well as a checklist to complete for each patient interaction. VHWs will receive ongoing supervision by means of bimonthly meetings with trained research staff and will attend a 1-day booster training session 2 months after the intervention begins to minimize drift in counseling skills. Typically, we audiotape counseling sessions to assess fidelity. However, in this setting, we will adapt an approach used by the Vietnam research for previous studies. At the start of each week, VHWs will provide a schedule of home visits to the research assistant (RA). The RA will observe a random selection of the counseling sessions and document delivery of essential components of the VHW protocol using a standardized scoring sheet.

### Evaluation plan

Mixed methods (i.e., qualitative interviews and survey) data will be collected from patients, providers, and VHWs. The evaluation plan is organized according to the following domains: primary outcome, secondary outcome, cost, baseline organization-level moderators, implementation process measures, and implementation fidelity.

### Outcome evaluation (AIM 1)

#### Primary outcome

To assess the primary outcome of provider adherence to tobacco treatment guidelines, we will conduct patient exit interviews (PEI) (surveys conducted immediately after the patient visit) with 50 smokers pre- and 50 post-implementation at each site (1300 in each study period) (Additional file 1) [35–38]. The PEI, completed immediately after the visit, assesses the full spectrum of PHS Guideline recommended care (i.e., 5As). It has well-established validity as evidenced by strong correlation with more costly audiotaped assessment of physician-patient interactions [35]. Prior to and approximately 12 months following each site’s enrollment, consecutive patients will be screened in the waiting area prior to seeing their provider, to determine smoking status and to obtain consent for the exit interview. The PEI will also assess readiness to quit and patient demographics. Patients are eligible to complete a PEI if they are (1) age 18 or over, (2) at the CHC for a routine patient visit, and (2) active smokers (current smoking within the past 7 days).

#### Secondary outcome

All patients who complete a PEI in the pre- and post-intervention period will be followed prospectively to assess 3- and 6-month 7-day point prevalence abstinence, defined as any smoking (even a puff) in the past 7 days [39]. Surveys will be conducted in person and smoking abstinence will be validated using carbon monoxide (CO) monitoring with abstinence defined as a CO < 10 ppm.

#### Cost analysis

Cost measures include implementation costs (e.g., VHW, system changes), patient time costs, and medical costs including model-estimated impacts on downstream costs attributable to tobacco-related illness (e.g., myocardial infarction). Health care and staff salary cost estimates will be derived from Vietnamese health ministry officials. Implementation costs will include health professional time requirements (including training of clinicians and VHWs), major constituents of the VHW intervention, and patient and provider materials. Incremental patient costs will be assessed by surveying additional patient time required by the VHW, as well as any indirect costs that are required (e.g., elder or child care). *Effectiveness inputs* for the simulation will arise from AIM 1 and will include 6-month smoking abstinence and changes in health-related quality of life as measured by the EQ-5D which has been translated into Vietnamese [40]. We will explore variable assumptions regarding the persistence of abstinence (e.g., relapse) in sensitivity analyses. Estimates regarding baseline disease incidence of chronic lung disease, lung cancer, and myocardial infarction, as well as lifetables describing all-cause mortality stratified by sex will be based on Vietnamese data.

#### Baseline organizational characteristics

##### Organizational structure and organizational readiness to change

At baseline, we are collecting data on organizational variables including number of FTE staff, staff characteristics, and clinic volume [28, 41]. We have also adapted a tool developed by Weiner et al., to assess baseline organizational readiness to implement practice guidelines [42]. These measures will be assessed using baseline surveys of medical directors at each CHC.

#### Implementation process evaluation (AIM 2)

We will use a mixed methods approach to assess outer setting (i.e., policies and resources) and inner setting constructs (e.g., climate, resources to support implementation, relative priority) that have been hypothesized to impact implementation outcomes. We have adapted a survey tool developed by Weiner et al., to assess implementation climate, and will use a measure developed by Solberg et al., to assess relative priority for implementing tobacco use treatment into routine practice [27, 43]. Baseline and post-intervention surveys (12 months) administered to clinical staff will assess these constructs. We will also conduct post-implementation semi-structured interviews with a sample of study staff participants in each site (2 VHWs, 3 providers, and 1 Medical Director) to further explore potential barriers and facilitators for tobacco use treatment as defined by CFIR. These include MOH policies, resources (staffing, funding, training), perceptions about the intervention (relative advantage, complexity), and beliefs about their own and their colleagues’ ability to provide effective tobacco use treatment (i.e., self and collective efficacy). The interview guides will also include questions about the process of integrating and customizing the implementation strategy into the CHC workflow as well as acceptability and potential for sustainability.

#### Implementation fidelity

We will use several approaches to evaluate the extent to which each component of the implementation strategies was delivered as intended.

##### Training and clinical reminder systems

RAs will conduct site visits at 2, 6, and 12 months to document (using a checklist) that the reminder and referral systems and other components of the toolkit (e.g., self-help brochures) materials are present and visible in the CHCs. We will record the percentage of staff that attends trainings, as well as any changes in staffing, and we will conduct brief pre- and post-training assessments.

##### Referral system

We will track the number of completed referral forms. We will measure the percentage of patients referred that were reached by the VHW and the number of contacts VHWs made with each patient contacted using VHW logs.

### Analysis plan

#### AIM 1

The primary outcome will be evaluated using mixed-effects regression analysis to estimate the difference between treatment conditions adjusting for the clustering effects across multiple levels (patients, providers, clinics) of the hierarchical data structure [44]. Treatment condition differences after the intervention period will be examined by creating a dummy variable for study arm with the TC condition as a reference category. The fixed-effects coefficient for treatment condition will contrast TCR and TC alone conditions after the intervention period. Covariates such as baseline organizational factors (guideline adherence, FTEs) and urban vs. rural site will be considered for inclusion in the mixed-effects model to reduce the within-group variance, if they are predictive of the primary outcome. A complex error term will be specified with intercepts randomly varying across sites and providers within sites. The secondary outcome is smoking cessation, a binary variable (scored 1 = Yes, 0 = No). We will conduct an intent-to-treat analysis (i.e., those lost to follow-up considered smokers). The basic model again involves a comparison of the two implementation strategies (TC vs. TCR). The binary outcome will be modeled by a generalized linear mixed-effects model similar to what was described above for the primary outcome [44]. A binomial family distribution and logit link will be used. Exponentiating the fixed-effects coefficient for treatment condition will generate an estimate of the odds ratio (i.e., the effect of treatment condition on the odds of patient smoking cessation).

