#### Power

For the primary outcome, optimal design [45] was used to estimate power to detect an effect size of one standard deviation. We assume 10 patients per clinician, 5 clinicians per site, and, conservatively, 33 % variance (i.e., the intra class correlation or ICC) at each level (site, clinician, patient). With 26 sites and assuming a two-sided type-1 error of 0.05, power is approximately 0.95 to detect this effect size. Optimal design was also used to estimate power for the secondary outcome, where an odds ratio of 2.3 is expected (13 % vs. 26 % abstinence for TC and TCR conditions, respectively) [5]. We assume a plausible interval for the smoking cessation rate among patients in the TC alone condition ranging from 0.01 to 0.25, and we assume conservatively that 50 % of the variability in cessation rates is between clinicians. With 26 sites, we have 80 % power to detect the estimated effect size.

Cost-effectiveness analysis (CEA): We will estimate the incremental cost-effectiveness (ICER) of ARM 2 compared to ARM 1 which is defined as the incremental change in costs divided by the incremental change in effectiveness (e.g., QALYs with TCR minus QALYs with TC alone). “QALY” refers to quality-adjusted life expectancy and is a quantitative measure that simultaneously takes into account both quality and quantity of life. We will use measures of effect based on analyses from this study combined with mathematical modeling to inform the derivation of the cost and QALY estimates over longer time horizons than those over which data will be collected (5-year, 10-year, 20-year, and lifetime horizons). Downstream impact of TCR on future costs and benefits (e.g., the downstream health impact of averting chronic lung disease, as well as the downstream costs averted by preventing those diseases) will be assessed via mathematical modeling using a Markov (“state-transition”) computer simulation that will enable attribution of the health benefit that would be caused by specified reductions in smoking [46–49]. We will perform the analysis from both a societal perspective and from a payer perspective [50].

#### AIM 2

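### Baseline adherence and other covariates enter the primary model only if they predict the outcome, so the model is settled on outcome data; the harm is modest and the remedy nearly free

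*Protocol article*

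**What the plan says.** All references are to the protocol article.

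- **Study design:** "The primary outcome is improvement in provider adherence to tobacco use treatment guidelines". The abstract and the Primary outcome section call the outcome provider adherence, without the word improvement.
- **Primary outcome:** exit interviews are planned with "50 smokers pre- and 50 post-implementation at each site (1300 in each study period").
- **Analysis plan, AIM 1, estimate:** "The fixed-effects coefficient for treatment condition will contrast TCR and TC alone conditions after the intervention period". The article states no period term, arm-by-period term, change score or committed baseline adjustment.
- **Analysis plan, AIM 1, covariates:** "Covariates such as baseline organizational factors (guideline adherence, FTEs) and urban vs. rural site" are candidates that "will be considered for inclusion in the mixed-effects model to reduce the within-group variance, if they are predictive of the primary outcome". The list is open, and neither a threshold nor a procedure is given.
- **Analysis plan, AIM 1, random effects:** "intercepts randomly varying across sites and providers within sites".
- **Power:** "optimal design [45] was used to estimate power to detect an effect size of one standard deviation", with 10 patients per clinician, 5 clinicians per site, about a third of the variance at each level, 26 sites and two-sided alpha 0.05. Stated power is approximately 0.95.

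**The concern.** The covariate sentence is a rule that the article states, not a detail left for later. A statistical analysis plan that follows it must look at the association of each candidate with the primary outcome before the primary model is known. Until then several models, and several p-values, are open for one primary test.

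The covariate most exposed is the one most likely to help. The comparison rests on 26 sites, and under the article's own variance components most of the variance of a site mean lies between sites. The site's own pre-implementation adherence is the natural covariate for that part, and the interviews that measure it are already planned. With so few sites, a screen can miss a useful baseline covariate by chance or admit an irrelevant one. Precision and, to a small degree, the nominal error rate are at stake.

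**Working it through.** **Inputs from the article.** Variance shares of 1/3 each for site, clinician and patient; 5 clinicians × 10 patients per site; 26 sites; two-sided alpha 0.05; effect of 1 SD.

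**Assumptions.** Allocation of 13 versus 13 sites (the ratio is not stated). Correlation r between a site's pre and post mean adherence of 0.3, 0.5 or 0.7 (not stated). For the selection rule, a p<0.05 screen on three site-level covariates, of which only baseline adherence is truly related to the outcome.

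**Step 1: reproduce the stated power.**

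- Variance of a site mean = 1/3 + (1/3)/5 + (1/3)/50 = 0.3333 + 0.0667 + 0.0067 = 0.4067. The between-site part is 0.3333/0.4067 = 82 %.
- Standard error of the arm contrast = √(4 × 0.4067/26) = 0.250.
- Noncentrality at 1 SD = 1/0.250 = 4.00. Noncentral t with 24 df gives power 0.969.

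This agrees with approximately 0.95 and uses no baseline covariate.

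**Step 2: always adjusting against never adjusting.** Adjustment for the site's baseline mean multiplies the variance by (1 − r²) and leaves 23 df.

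| | Unadjusted | r = 0.3 | r = 0.5 | r = 0.7 |
|---|---|---|---|---|
| Power at 1 SD | 0.969 | 0.980 | 0.993 | >0.999 |
| Power at 0.75 SD | 0.820 | 0.853 | 0.912 | 0.980 |
| Power at 0.5 SD | 0.484 | 0.519 | 0.599 | 0.764 |
| Effect detectable at 80 % power (SD) | 0.73 | 0.70 | 0.63 | 0.52 |

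These differences are the loss if baseline adherence is left out. They are not the cost of the article's rule, which sometimes lets it in.

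**Step 3: the rule against pre-specification.** I simulated 26 site means at 0.75 SD (8,000 runs per row). The two figures for the rule are for a screen that ignores arm and a screen with arm in the model.

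| r | Unadjusted | Rule | Pre-specified | Largest loss |
|---|---|---|---|---|
| 0.3 | 0.813 | 0.805 / 0.833 | 0.834 | 0.029 |
| 0.5 | 0.817 | 0.862 / 0.897 | 0.903 | 0.041 |
| 0.7 | 0.819 | 0.965 / 0.975 | 0.977 | 0.012 |

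The pre-specified column lies slightly below Step 2 because the simulation includes chance baseline imbalance between arms. A repeat at 0.5 SD gave losses within the same limit.

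With the screen that ignores arm, baseline adherence was selected in 24–33 % of trials at r = 0.3, 61–77 % at r = 0.5 and 92–99 % at r = 0.7. The range runs over the null and the 0.75 SD effect.

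**Step 4: type I error of the rule.** In 20,000 null runs per setting, with r from 0 to 0.7, it was 0.047–0.051 when the screen ignored arm and 0.051–0.060 when arm was in the screening model. Repeat runs reached about 0.063.

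**The case against.** The strongest defence is that the rule largely corrects itself. It names guideline adherence first among the candidates and tends to admit it when it is strongly predictive, which is when it matters. Step 3 bears this out: the loss is small throughout, and at r = 0.7 it is at most about one point. The threshold and the number of candidates in that step are mine, and an analysis plan might set a milder procedure. Lower correlations are also plausible: both arms receive training and reminders between the two surveys, about 12 months pass, and staff may change. All of this limits the size of the point. It does not answer the objection to choosing the primary model on the primary outcome, because the article itself states that criterion.

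A reader might infer four stronger things that the article does not support.

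- **That the Step 2 gap is the price of the plan.** It compares always with never adjusting, and the article does not say never.
- **That a post-period contrast is invalid for an outcome worded as improvement.** Under randomisation the arms share the same expected baseline, so the post-period difference is unbiased for the difference in improvement. The wording should be aligned, but validity is not affected.
- **That reducing within-group variance is a mistaken reason, because a site-level covariate acts between sites.** The group can be read as the treatment arm, and variance within an arm includes variance between sites.
- **That the baseline data are already in hand.** Trial status reports 398 interviews for Wave 1 and 401 so far for Wave 2, so 799 of the planned 1300. They are planned, not complete.

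**Conclusion.** The point holds in a limited form. The article fixes a rule under which the primary model depends on the outcome data, and it does not commit to the one baseline covariate that the design already plans to measure at every site. Under the assumptions above, the rule costs about 0 to 4 power points against pre-specified adjustment at 0.5 to 0.75 SD, with type I error of about 0.05 to 0.06. The larger loss, with power at 0.5 SD of 0.48 instead of 0.52 to 0.76, follows only if baseline adherence is left out.

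The trial is not underpowered on this account: the planned 1 SD effect has power 0.969 without any adjustment. The sizes rest on r and on the screening procedure, neither of which the article gives. That selection depends on the outcome rests on the text alone. This is a nearly free improvement, not a flaw that threatens the result.

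**What to change.** Replace the covariate sentence in Analysis plan, AIM 1, with:

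*The primary model includes the site's pre-implementation mean adherence score as a fixed, pre-specified covariate (or models pre and post interviews jointly with a common baseline mean and a site-by-period random effect). No covariate is selected on its association with the outcome.*

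Report the unadjusted model and any further-adjusted models as sensitivity analyses. Align the improvement wording in Study design with this estimate. A plain change score is not a good way to do so: its variance is 2(1 − r) times that of the post-period mean, which is larger whenever r is below 0.5. At r = 0.3 it would lower power at 0.75 SD from 0.820 to 0.681.

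The cost is one of 24 degrees of freedom and a change of wording. No data are needed beyond the interviews already planned. Trial status places the Wave 1 post-intervention interviews still ahead, so at the time of the article the change could be made before any post-intervention outcome was analysed.
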